#### Pain pressure threshold (PPT)

PPT will be determined by applying blunt pressure by a hard-rubber probe, using an approved device (EMG 1630WF, EMG System, Brazil). During the test, pressure will be applied to the same area as in the mechanical perception and pain threshold tests, with increasing intensity at a rate of 1 kg/second. When the subject reports that he/she feels any pain, the procedure will be stopped. A computer program (EMGLab, EMG System, Brazil) will automatically record the value. This procedure will be repeated three times to achieve an average.

These tests will take approximately 7–10 minutes to be completed.

#### Electroencephalogram (EEG)

The EEG is a powerful tool to assess changes related to anxiety [29]. It will measure the brain’s electrical current intensity, using the analysis of alpha and theta waves. Alpha waves are related to physical relaxation and are higher when the subject keeps his/her eyes closed. Alpha power density is reduced when the eyes are open. The same can be seen in relaxation and alertness respectively. Theta waves are related to awareness states and are higher chronic pain conditions.

For this study, a 32-channel EEG (BrainNet BNT 36, EMSA, Brazil) will be used. Data will be band pass filtered (0.5 to 50 Hz) and acquired at 200 Hz. The channel location will be used according to the International 10–20 EEG System. Wave power and frequency will be checked before and after tDCS stimulation. The reference electrodes will be located at Cz. The data will be analyzed in MATLAB (The Mathworks, Inc., Natick, MA, USA). After signal filtering, data will be epoched into 1.28-second segments to standardize artifact removal. Artifacts will be removed using EEGLab (the semi-automated rejection EEGLab). Epochs containing extreme values (above −750 and below 750 μV) will be rejected using independent component analysis (ICA), removing the first component. After artifact removal, a frequency analysis will be run based on the following band widths: a) theta (4–8 Hz), b) alpha (8–12 Hz), and c) beta (13–30Hz).

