### Outcomes

The primary outcome of this study will be the extent to which this method will change baseline pain intensity (VAS). The subjects will record their experience on a daily basis in a pain diary. A weekly response average will be calculated before the first intervention and after each session. The averages will be used to compare the VAS values before and after each intervention. A decrease of 50 % will be considered a satisfactory clinical improvement.

Secondary outcomes will be the degree of change from baseline in power density of alpha and theta EEG bands. Other outcome measures will be pain pressure threshold (PPT), mechanical pain thresholds (MPTs), and STAI. Increase in PPT and mechanical thresholds indicate an improvement in subject pain condition; a decrease in STAI indicates a better emotional state.

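### The EEG cleaning rule defines extreme values as the normal range and removes an ICA component by position, so the alpha and theta change outcome could be distorted

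*Protocol article*

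**What the plan says.** The rule stands in the protocol article under Procedure details, Electroencephalogram (EEG). The signal is described first: "Data will be band pass filtered (0.5 to 50 Hz) and acquired at 200 Hz", and after filtering "data will be epoched into 1.28-second segments to standardize artifact removal". The cleaning tool is named next: "Artifacts will be removed using EEGLab (the semi-automated rejection EEGLab". The rule itself follows: "Epochs containing extreme values (above −750 and below 750 μV) will be rejected using independent component analysis (ICA), removing the first component". The band analysis comes last: "After artifact removal, a frequency analysis will be run based on the following band widths", namely theta, alpha and beta.

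The Outcomes section shows what depends on this step: "Secondary outcomes will be the degree of change from baseline in power density of alpha and theta EEG bands". Aims 3 to 5 use the same EEG data (change from before to after stimulation, association with pain and anxiety, comparison of 1 mA with 2 mA). So do the correlations of clinical with EEG data in Statistical methods.

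**The concern.** The sentence has three separate defects.

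- **The limits.** The bracket is meant to define extreme values, but it describes the interval between −750 and +750 μV, where ordinary values lie.
- **Two operations in one.** Rejecting an epoch discards a stretch of time. Removing an ICA component subtracts one source from the data that are kept. An amplitude limit is not applied by means of ICA, so the reader cannot tell which step is done or in what order.
- **Selection by position.** The component to be removed is fixed as the first. Nothing requires it to be ocular or muscular, and nothing ensures that the first component is the same source in the two recordings of a session.

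The third defect matters most. The outcome is a change between two recordings. If the subtracted source differs between them, part of the measured change in alpha or theta power comes from the cleaning and not from the stimulation.

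**Working it through.** The protocol gives no figure that depends on this rule, so there is none to reproduce. The checks below show what the rule does under each reading.

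**Inputs from the article.** Epoch length 1.28 s, sampling rate 200 Hz and limits of ±750 μV (EEG section); 15 subjects (Sample size); EEG before and after stimulation at three sessions (Table 1).

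**Inputs assumed.** The article gives no signal amplitude. Samples are taken as independent and normal with mean zero, with SDs from 10 to 300 μV. The shares of alpha power used in step 4 are also assumed.

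**1. Scale.** Samples per epoch: 1.28 × 200 = 256. Recordings passing through the rule: 15 × 3 × 2 = 90.

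**2. Literal reading.** Let p be the probability that one sample lies between −750 and +750 μV. An epoch is rejected if it contains at least one such sample, with probability 1 − (1 − p)^256. This is 1.000 for every assumed SD from 10 to 300 μV. Essentially every epoch is rejected, including those that also contain an extreme sample.

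**3. Evident intent.** If an epoch is rejected when any sample lies outside the limits, the probability is 1 − p^256:

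| Assumed SD (μV) | p | Epochs rejected |
|---|---|---|
| up to 100 | 1.0000 | about 0% |
| 200 | 0.99982 | 4.4% |
| 300 | 0.98758 | 95.9% |

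How much the amplitude screen removes therefore depends on amplitudes that the article does not give. At the lower assumed SDs it removes almost nothing, and the cleaning then rests mainly on the ICA step.

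**4. Positional removal.** Suppose true alpha power does not change, and the removed component carries a share s_pre of alpha power before stimulation and s_post after it. The apparent relative change is (1 − s_post)/(1 − s_pre) − 1.

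| s_pre | s_post | Calculation | Apparent change |
|---|---|---|---|
| 0 | 0.20 | 0.80/1.00 − 1 | −20% |
| 0.20 | 0 | 1.00/0.80 − 1 | +25% |
| 0.50 | 0.20 | 0.80/0.50 − 1 | +60% |
| 0.20 | 0.20 | 0.80/0.80 − 1 | 0% |

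Equal shares leave the relative change unbiased. The rule contains nothing that keeps them equal. The table shows the mechanism and does not estimate what this trial would see.

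**The case against.** The best defence is that this is one clumsy sentence about a secondary outcome. The word for extreme values makes the intended limit plain, and an analyst who applied the bracket literally would be left with no data and would see the error at once. This stands: the inversion alone is a slip.

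A second defence is that the procedure is called semi-automated, which leaves room for an operator to judge components. This stands only in part. No operator criterion is given, and the next sentence says which component goes: "will be rejected using independent component analysis (ICA), removing the first component". If judgement was intended, the text contradicts it.

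A third defence is that the same processing applies to sham, 1 mA and 2 mA within each subject, and that a blinded biostatistician analyses the data. Cleaning error unrelated to condition would then mainly add noise and would not favour one condition. This is fair, and it limits the claim. It does not help the comparison of before with after within a condition, and added noise is itself a cost with 15 subjects.

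A fourth defence is that an article may leave component criteria to a fuller document. That would answer a complaint about missing detail. Here a rule is stated, and it is the stated rule that is at fault.

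A reader might also infer more than the article supports:

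- **That extreme epochs would be kept and ordinary ones lost.** Step 2 shows that nearly all epochs would go.
- **That alpha itself would be subtracted because recordings are made with eyes closed.** The article says "Alpha waves are related to physical relaxation and are higher when the subject keeps his/her eyes closed", but this is general background, the next sentence concerns open eyes, and no recording condition is fixed. Nor does the article say how components are ordered, so first cannot be taken to mean largest.
- **That ±750 μV is too lenient and needs a new limit.** The article gives no amplitudes from which to judge this, and a generous gross limit followed by ICA is a coherent design.

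**Conclusion.** The point holds in a limited form. The bracket contradicts the term it defines and must be corrected, although its intent is clear. The substantive defect is the removal of a component by position with no artefact check, and this remains after the signs are put right. It could distort the change in alpha and theta power, or make it noisier, and the same applies to the EEG parts of aims 3 to 5.

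It would go too far to say that the EEG outcome will be computed on wrongly cleaned data. Bias requires that the removed component carry alpha or theta power and that its share differ between the two recordings, and the article settles neither. All 90 recordings pass through the step, but none is shown to be distorted. The size of the effect cannot be derived from the document. The VAS primary outcome, the sample size, the power and the alpha level are untouched.

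**What to change.** Replace the sentence with two separate steps, in a stated order:

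1. Epochs with any sample below −750 μV or above +750 μV (or whatever limit was intended) are rejected.
2. ICA components are removed only when they meet pre-stated criteria for ocular or muscle artefact. The criteria are judged blind to condition and to whether the recording was made before or after stimulation, and are applied identically to all recordings.

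Delete the instruction to remove the first component. If the semi-automated procedure was meant to include operator review, say so here. The reviewer should be someone without access to the randomisation list, and the files should be coded so that timing is hidden.

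The cost is a wording change and a brief blinded component review of up to 90 recordings, which the existing team should be able to do. No visit, measurement or sample size changes.

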### Safety monitoring

At each stimulation session, subjects will complete a questionnaire to evaluate potential adverse effects of tDCS (tingling, burning sensation, headache, neck pain, mood alterations) on a 5-point scale. Subjects will be asked whether they experienced any side effects in an open-ended manner, and they will be specifically asked about headache, neck pain, scalp pain, burning sensations, tingling, skin redness, sleepiness, trouble concentrating, and acute mood change.

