An advantage of tDCS is that it has minimal side effects. The most common adverse effects are itching, tingling, and mild headache that resolve just after the stimuli is terminated. These adverse effects depend on the intensity and duration of the treatment session. The most common protocols use a lower intensity (1 or 2 mA) with a treatment session duration of 20 or 30 minutes. To access tolerability and safety of tDCS, a side effect questionnaire has been developed [19].

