### Intervention C

This will be the sham intervention. Stimulation electrodes will be placed at the same areas as for interventions A and B, but the current will be applied only for the first 30 seconds, after which it will be reduced gradually until it reaches zero. This method has been shown to be effective in previous studies [21].

In all the intervention groups, tDCS will be applied using 35 cm^2^ (5×7 cm) sponge electrodes soaked in saline solution (140mMolNaCl, water dissolved in Mille-Q). Anodal and cathodal electrodes will be connected in the tDCSdevice (Soterix Medical 1 × 1 tDCS 1300A, USA). Two 9-V batteries will deliver current.

All subjects will receive only one stimulation session for each type of intervention (IA, IB and IC), for a total of three sessions. After each tDCS session, the subject will complete a questionnaire to record any adverse affects. A trained researcher ([name]) will perform each procedure. One researcher who is responsible for the general supervision ([name]) during testing will hold the randomization list, and only the clinician responsible for the tDCS stimulation will know which intervention group is being applied. All clinical and neurological assessments will be performed at the Functional Electrostimulation Laboratory at Federal University of Bahia (Salvador, Brazil).

As this is a crossover study with only four weekly sessions, we believe that there will not be a compliance problem. Furthermore, since side effects are minimal, there is a low risk of dropouts due to this reason.

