### Technical and scientific resources

The two important goals of this research are to establish the most effective protocol for tDCS and to demonstrate a therapy that may be useful for TMD patients. The use of tDCS for TMD is feasible in clinical practices that have many patients presenting with this disorder. tDCS is noninvasive, low cost, and easy and rapid to implement. Further, this treatment has minimal adverse effects.

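### Itching is named among the most common tDCS adverse effects but is on neither the graded nor the prompted adverse-effect list

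*Protocol article*

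**What the plan says.** The Background section of the protocol article states: "The most common adverse effects are itching, tingling, and mild headache that resolve just after the stimuli is terminated". It adds: "These adverse effects depend on the intensity and duration of the treatment session".

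Under Intervention C, the purpose of the form is given broadly: "After each tDCS session, the subject will complete a questionnaire to record any adverse affects".

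The Safety monitoring section gives the content in three parts:

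- a questionnaire at each stimulation session, with five effects in brackets: "tingling, burning sensation, headache, neck pain, mood alterations) on a 5-point scale";
- an open question: "Subjects will be asked whether they experienced any side effects in an open-ended manner";
- a set of direct prompts: "they will be specifically asked about headache, neck pain, scalp pain, burning sensations, tingling, skin redness, sleepiness, trouble concentrating, and acute mood change".

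**The concern.** One section says which effects are most to be expected, and another says which effects subjects will be asked about. The two do not match. Staff who follow the Safety monitoring text would ask every subject about tingling and headache after every session, and would ask nobody about itching. Effects that the protocol groups together would then be collected in two different ways, and their recorded frequencies could not be set side by side.

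Current intensity is the experimental factor here, and the Background says that adverse effects vary with it. A description of how each condition was tolerated would therefore be natural to report, and for itching it would rest on spontaneous mention alone. An effect that was not asked about at a session, and that the Background expects to fade once stimulation ends, is hard to recover afterwards.

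A second, smaller matter is the 5-point scale. It is attached to the five bracketed effects, and the text does not say whether it also applies to the prompts outside that bracket.

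**Working it through.** The plan gives no figure to reproduce, and no formula applies. The check is an item-by-item comparison of the Background section with the two lists in Safety monitoring.

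| Effect | Named as most common (Background) | Five effects on the 5-point scale | Nine specific prompts |
|---|---|---|---|
| Itching | yes | no | no |
| Tingling | yes | yes | yes |
| Headache | yes (mild) | yes | yes |
| Burning | – | yes | yes |
| Neck pain | – | yes | yes |
| Mood change | – | yes | yes |
| Scalp pain | – | no | yes |
| Skin redness | – | no | yes |
| Sleepiness | – | no | yes |
| Trouble concentrating | – | no | yes |

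From the table:

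1. Effects named as most common: 3. On both lists: 2. On neither: 3 − 2 = 1, which is itching.
2. All five graded effects reappear among the nine prompts (taking the two mood entries as the same item), so the shorter list is nested in the longer one. Prompts outside the graded list: 9 − 5 = 4.
3. Distinct items once itching is added: 9 + 1 = 10.
4. Forms concerned: 15 subjects × 3 sessions = 45. This counts questionnaires, not lost events.

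The under-count cannot be computed. If itching occurred in k of the 45 sessions and a share r of those were volunteered, the open question would record r × k. The documents give neither k nor r. The recorded number could lie anywhere from 0 (r = 0) to k (r = 1).

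**The case against.** The strongest reply is that this is a condensed article and the form itself is not shown. The Background mentions that a side-effect questionnaire for tDCS exists, and the real form may include itching. The bracketed five effects can be read as examples. The form is meant to record any adverse effect, and the open question gives itching a route into the data.

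Part of this stands. Itching is not shut out, and the five-item bracket may be illustrative. But the nine prompts are stated without any wording that marks them as examples, and they extend to sleepiness and concentration while leaving out one of the three effects the article itself calls most common. The article does not say that the questionnaire mentioned in the Background is the one used. This is a mismatch between two stated passages, not a detail left to a fuller document. The open question softens the gap without closing it, because tingling and headache get a prompt and a grade as well.

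A reader might infer several stronger points that the documents do not support:

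- **A planned tolerability comparison is compromised.** None is planned. The Aims compare 1 mA and 2 mA on pain, anxiety, stress and EEG, and neither Study variables nor Statistical methods names adverse effects.
- **The two lists contradict each other.** They differ in length, but the five are contained in the nine.
- **Four prompted effects have no grade.** The text is silent on this, so it is only one possible reading.
- **Skin sensation, and with it a cue to sham versus active current, goes unmeasured.** Tingling and burning are on both lists, and scalp pain and skin redness are prompted.
- **The trial's safety claim rests on a deficient form.** The statement under Technical and scientific resources, "Further, this treatment has minimal adverse effects", describes the technique in advance and is not a conclusion from these data.
- **Itching is the leading effect.** It comes first in a list of three that carries no frequencies or ranking.

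**Conclusion.** The point holds as a minor one. As the text stands, 1 of the 3 effects named as most common is neither prompted nor listed for grading, and for 4 of the 9 prompts it is unclear whether a grade is recorded. Itching can still enter the data, but only through spontaneous report.

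The conclusion assumes that staff follow the prompts as written. That spontaneous report captures less than a direct prompt is a reasonable expectation, but nothing in the documents measures it, so no size can be put on the loss. The sample size, the primary VAS analysis and the planned secondary analyses are unaffected.

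**What to change.** Replace the two lists in Safety monitoring with a single list of ten items: the nine existing prompts plus itching. State that every item is graded on the same 5-point scale at each session. Keep the open-ended question for anything else. Say that the grades will be tabulated descriptively by condition (sham, 1 mA, 2 mA), without a formal test.

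The cost is a slightly longer form at each of the 45 planned sessions, with no extra visits, staff or subjects. The reported frequency of adverse effects may rise, because itching would now be asked about. The article states that recruitment is under way, so any sessions completed on the existing form should be identified in the tabulation, since itching was collected differently in them.

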### Study variables

The dependent variables will be (1) VAS for pain intensity, (2) STAI, (3) quantitative sensory testing, and (4) EEG quantitative analysis. The independent variables will be (1) cathodal tDCS over DLPFC (1 mA and 2 mA) and (2) sham treatment.

### Statistical methods

The data will be recorded and analyzed by a blinded biostatistician. First, a descriptive analysis of variables will be performed. Data distribution will be analyzed using the Shapiro-Wilk test. To check carryover effects between sessions, we will carry out a *t*-test or a Wilcoxon rank sum, depending on the normal distribution.

Outcome measures will be compared both between and within groups considering pre- and post-interventions with repeated measures analysis of variance or nonparametric correspondence tests (Friedmann and Mann–Whitney tests). Clinical data will be correlated to EEG data through correlation tests (Spearman or Pearson). Significance will be established at an alpha value of 5 %, with a study power of 80 %. All data will be analyzed with intention-to-treat.

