### Sample size

Following IMMPACT (Initiative on Methods, Measurement, and Pain Assessment in Clinical Trial) [25] recommendations for clinical trials involving chronic pain, we considered our primary outcome measure to be pain intensity changes, assessed through a VAS. We achieved a sample size of 15 subjects (G*Power 3.1), considering a reduction of 50 % (effect size of 0.5), a study power of 80 %, an alpha value of 5 % (*P* < 0.05), and six measures (three pre- and post-measures) on three intervention groups (placebo, and tDCS 1 mA and 2 mA).

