### Data collection procedure

After COAT institutional authorization, subjects will be contacted by phone to ascertain their interest. All interested participants will complete a pre-screening questionnaire. Each subject will be scheduled for an appointment in order to further determine if they meet the inclusion criteria. If they do, they will sign an informed consent and be formerly enrolled in the study.

Women of childbearing age will be required to take a urine pregnancy test during the screening process. If a subject becomes pregnant during the course of the study, she will be withdrawn. During this initial appointment, the subject will be asked to complete a daily pain VAS diary for 7 days. The average VAS score from this data will be used as a baseline pain value.

During a second visit (T2) all clinical and neurological assessments will be performed before and after the tDCS stimulation. The clinical assessments will be measured by VAS pain scores, anxiety measures, and quantitative sensory tests. Neurophysiological assessment will be measured by using an EEG to analyze cortical activity. Each patient will be clinically and neurologically assessed before and after the treatment session resulting in six data collection points (T2 to T7).

All subjects will be treated during a single session for three different interventions (IA, IB,or IC) with a washout period of 7 days between treatments in order to avoid any residual effects. As reported earlier, a single tDCS session usually is able to modify cortical excitability for 1 hour after stimulation [22, 23].

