#### Visual analog scale (VAS) for pain

The VAS allows us to convert subjective sensations, such as pain, into numerical data. A 10-cm scale, where 0 cm is no pain and 10 cm is the worst imaginable pain, will be used, and the subjects will be asked to mark a point on the scale representing their pain intensity. This instrument will be completed everyday in the 7-day period after their acceptance. An average pain intensity score will be calculated as a baseline for the first treatment intervention. Averages for each week will be used to analyze if there will be any treatment carryover effect. The VAS scores will be recorded before and after each treatment session to verify treatment effect.

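### For outcomes measured before and after each tDCS session, the repeated-measures ANOVA in effect compares change scores; adjusting for the pre-session value would usually be more precise at almost no cost

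*Protocol article*

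**What the plan says.** The Statistical methods section of the protocol article gives the analysis in one sentence: "Outcome measures will be compared both between and within groups considering pre- and post-interventions with repeated measures analysis of variance". Friedman and Mann-Whitney tests are the fallback. Neither route includes a covariate.

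The pre-session values are treated as outcome measurements throughout. The Sample size section bases the 15 subjects on "six measures (three pre- and post-measures) on three intervention groups", and the Data collection procedure section counts six assessment points, T2 to T7, one before and one after each of the three sessions.

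Table 1 shows VAS, sensory testing and EEG both pre- and post-tDCS at every treatment visit. On the in-session VAS the protocol says: "The VAS scores will be recorded before and after each treatment session to verify treatment effect". Table 1 lists the anxiety inventory once per visit without separating pre from post, so it is left out here.

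The primary outcome is a different quantity. Under Outcomes it is the weekly average of a daily pain diary, taken before the first intervention and after each session.

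**The concern.** If pre and post are two levels of the outcome, the test of whether active stimulation differs from sham is the interaction of intervention with time. That is the same as comparing post-minus-pre changes between interventions, which fixes the slope on the pre-session value at 1.

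Stable differences between patients already drop out of a crossover. What remains in the pre-session value is visit-to-visit variation, which the post-session value shares only in part. Subtracting all of it adds noise to the contrast.

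At stake is the precision of the active-versus-sham and 1 mA-versus-2 mA comparisons on in-session pain, thresholds and EEG. Only 15 patients carry these, and the Ethical aspects section says participants will later be offered the protocol that performs best.

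**Working it through.** **1. The plan's own figure.** The inputs stated under Sample size are an effect size of 0.5, alpha 5%, power 80%, three interventions, and pre and post measures. I read 0.5 as Cohen's f, the G*Power metric for ANOVA. For the group-by-time interaction with k = 3 groups, m measures and correlation ρ among them, λ = f²Nm/(1−ρ), df1 = (k−1)(m−1), df2 = (N−k)(m−1).
- m = 2 (pre, post), ρ = 0.5 (assumed): N = 14, or 15 with three equal groups; power at 15 is 0.87.
- m = 6, ρ = 0: N = 13, or 15 with equal groups.
- m = 6, ρ = 0.5: N = 8, or 9 with equal groups.
- One group, three-level within factor, ρ = 0: N = 15.

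So 15 is compatible with a pre/post interaction, but other set-ups also give it.

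**2. Variance of the two analyses.** Let r be the same-session pre-post correlation after patient means are removed, with equal pre and post variances. The variance of a treatment contrast is proportional to
- 2(1−r) for change scores;
- 1−r² for covariate adjustment with a known slope.

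The ratio is (1−r²)/[2(1−r)] = (1+r)/2. The slope has to be estimated. With 15 patients and three sessions, the change-score model has (15−1)(3−1) = 28 residual degrees of freedom, and estimating the slope inflates the variance by about 1 + 1/26 = 27/26. The working ratio is (1+r)/2 × 27/26, which reaches 1 at r = 2 × 26/27 − 1 = 0.93.

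**3. What r might be.** The protocol gives no SD or correlation, so r is an assumption. It is lower than a raw pre-post correlation because the crossover has already removed patient differences: r = (same-session − between-session)/(1 − between-session). For example, a raw 0.7 with between-session 0.5 gives 0.2/0.5 = 0.4.

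**4. Power.** A standardized contrast of 0.749 gives the change-score analysis 80% power (n = 15, two-sided 5%, 28 df; noncentrality 0.749 × √15 = 2.90). For adjustment, divide 2.90 by the square root of the ratio and use 27 df.

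| r | Ratio | Noncentrality | Power, adjusted | Power, change |
|---|---|---|---|---|
| 0.3 | 0.65 × 27/26 = 0.675 | 3.53 | about 93% | 80% |
| 0.5 | 0.75 × 27/26 = 0.779 | 3.29 | about 89% | 80% |
| 0.7 | 0.85 × 27/26 = 0.883 | 3.09 | about 85% | 80% |
| 0.8 | 0.90 × 27/26 = 0.935 | 3.00 | about 82% | 80% |
| 0.9 | 0.95 × 27/26 = 0.987 | 2.92 | about 80% | 80% |

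Simulation of a 15 × 3 crossover with patient fixed effects agrees. Variance ratios were 0.93 at r = 0.8, 0.99 at 0.9 and 1.01 at 0.95, and type I error was near 5% for both methods. At r = 0.5 the gain equals 15/0.779 = 19.3 patients' worth of information from 15.

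**5. The diary outcome.** With one baseline week B per patient, the active-minus-sham difference in change is (A−B)−(S−B) = A−S. The baseline cancels, and as a covariate it would be absorbed by the patient effect, so the gain is zero. If the preceding week is used instead, the 7-day spacing makes the week before sessions 2 and 3 the outcome week of the previous intervention. That covariate may already carry a treatment effect.

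**The case against.** The strongest reply has four parts.

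- **The model is inferred.** The Statistical methods section does not mention an interaction or change scores, and the sample size does not identify one model. This stands as a caution. However, the section does name the method and compares interventions on pre and post values with no covariate, and the change comparison is the natural between-intervention test in that layout.
- **The planned test is valid.** This stands. A reader might infer that the planned ANOVA is biased or has the wrong error rate. Nothing supports that: order is randomized and type I error is near 5% either way.
- **Change is what the protocol wants to know.** Aim 3 asks about pre-to-post change in EEG, and Outcomes defines the EEG endpoint as change from baseline. This stands for the within-intervention comparisons, which should be kept. It does not decide how interventions are best compared with each other, since both analyses estimate the same treatment difference.
- **r may be high.** Pre and post fall within one visit of about 3 hours. This cannot be excluded, and at r of about 0.9 nothing is gained. The textbook statement that adjustment wins for every r below 1 ignores slope estimation and is too strong with 15 patients.

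**Conclusion.** The point holds for outcomes measured before and after stimulation at each session: in-session VAS, pressure and mechanical pain thresholds, and alpha/theta power. For these the planned between-intervention test is valid but usually less precise than covariate adjustment. The gain is worthwhile at low to moderate r (about 13 points of power at r = 0.3 and 9 at 0.5), modest at 0.7 to 0.8 (about 5 and 2), and absent from about 0.9.

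These figures rest on an assumed r, equal pre and post variances, and an 80% starting power set by calibration rather than derived from protocol variances. A reader might infer that the trial's primary comparison loses this power. It does not: the primary outcome is the weekly diary average, where a common baseline cancels within patient and a preceding-week baseline is the previous intervention's outcome week.

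**What to change.** For the active-versus-sham and 1 mA-versus-2 mA contrasts on in-session VAS, pressure and mechanical pain thresholds, and alpha/theta power, model the post-session value with:
- treatment;
- patient, as a fixed effect, or as a random effect with the patient's mean pre-session value also in the model;
- that session's pre-tDCS value as covariate.

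Report adjusted differences with 95% confidence intervals. Retain the within-intervention pre-to-post comparisons as descriptive or supporting results. State that this covariate is not applied to the weekly diary average.

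The cost is a change of wording and one residual degree of freedom. Every value needed is already scheduled in Table 1.
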